The sample size was calculated based on the co-primary outcome of 7-day point prevalence abstinence (PPA) at week 6. Referring to recent systematic reviews of acupuncture smoking cessation trials (21, 22), a control group abstinence rate of approximately 15% was assumed, with an odds ratio (OR) of 1.9 for the HMA + NRT group. With a two-sided significance level of *α* = 0.05, 80% power, and a 1:1 allocation ratio, a total of 188 participants is required. Accounting for a 15% dropout rate, the final sample size is set at 220 participants (110 per group) (23). The VAS craving outcome, as the other co-primary endpoint, is also adequately powered based on the same sample size. Multiplicity control. Because two co-primary outcomes are designated, the overall type I error rate is controlled using the Hochberg procedure. Under this approach, each outcome is tested at the full *α* = 0.05 level; the family-wise error rate is preserved because the trial is considered positive only if both co-primary outcomes achieve statistical significance (*p* ≤ 0.05 each). This method offers greater power than Bonferroni correction while maintaining strong control of the family-wise error rate.

To monitor expectancy and attention effects, participants will complete the Credibility/Expectancy Questionnaire (CEQ) at baseline and post-randomization; these scores will be explored in sensitivity analyses (16).

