### Limitations

3.1

This study has several limitations. First, the single-center design and relatively strict inclusion and exclusion criteria, including the exclusion of individuals with severe psychiatric comorbidities, may limit the generalizability of the findings to broader populations of smokers with tobacco use disorder.

Second, the absence of a sham acupuncture or attention-matched control limits the ability to distinguish specific effects of harmonizing mind acupuncture (HMA) from nonspecific or placebo-related effects, particularly for subjective outcomes such as visual analog scale (VAS) craving, BDI-II, and BAI scores. However, this design reflects the pragmatic objective of the trial to evaluate effectiveness in real-world clinical settings, and comparison with standard care (NRT alone) remains appropriate for informing clinical decision-making. To partially address this concern, biochemically verified 7-day point prevalence abstinence (PPA) has been included as a co-primary outcome, providing an objective measure of cessation that is less susceptible to expectancy effects. Differences in treatment exposure between groups may introduce attention-related bias, although baseline and post-randomization treatment expectancy scores will be collected and incorporated into sensitivity analyses to mitigate this effect.

Third, the 24-week follow-up period may be insufficient to fully capture long-term relapse patterns; future studies should consider extended follow-up durations of at least 52 weeks to better assess sustained abstinence and relapse risk.

Fourth, the technical complexity of the HMA protocol and the requirement to elicit De Qi sensations may introduce inter-practitioner variability despite standardized training and detailed procedural manuals.

Fifth, although missing smoking-status data will be handled as non-abstinent in the primary analysis, sensitivity analyses using MNAR assumptions may still be biased if dropout is related to unmeasured factors such as relapse or adverse events.

Sixth, while the sample size of 220 provides adequate power for both co-primary outcomes (VAS craving change and biochemically verified PPA), the single-center design and relatively strict inclusion criteria may still limit generalizability. Future multicenter studies with more diverse populations are warranted to confirm the findings.

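### The stated total of 188 does not follow from its own inputs: 15% control abstinence and OR 1.9 need about 490 evaluable participants, and 188 gives about 41% power

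*Protocol article*

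**What the plan says.** Section 2.3 of the protocol article names the sizing outcome: "The sample size was calculated based on the co-primary outcome of 7-day point prevalence abstinence (PPA) at week 6". It gives the planning values: "a control group abstinence rate of approximately 15% was assumed", "with an odds ratio (OR) of 1.9 for the HMA + NRT group". The test is two-sided at 0.05, and the result is "80% power, and a 1:1 allocation ratio, a total of 188 participants is required". The allowance for losses follows: "Accounting for a 15% dropout rate, the final sample size is set at 220 participants (110 per group".

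The other co-primary outcome is covered by one sentence: "The VAS craving outcome, as the other co-primary endpoint, is also adequately powered based on the same sample size". Section 3.1 (Limitations) repeats that "the sample size of 220 provides adequate power for both co-primary outcomes".

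Two further rules bear on power. Sections 2.3 and 2.10.1 call the trial positive only if craving and PPA are both significant at 0.05. Section 2.10.1 counts missing smoking status as non-abstinent in the primary analysis.

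**The concern.** All the inputs to a two-proportion sample size are printed, so the result can be checked directly. A difference of about ten percentage points from a 15% base ordinarily needs more than 200 participants per arm, and 94 per arm is far below that.

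PPA is the outcome on which the trial's credibility rests. Participants are unblinded and craving is self-reported, and section 3.1 presents biochemically verified abstinence as the safeguard against expectancy effects. If power on that outcome is about half of what is claimed, a true effect of the planned size is more likely to be missed than found. A non-significant PPA result could then be taken as evidence of no effect because the article describes the trial as adequately powered.

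**Working it through.** **Inputs (all from section 2.3).** Control rate p1 = 0.15; OR = 1.9; two-sided alpha 0.05 (z = 1.960); power 80% (z = 0.842); allocation 1:1; stated requirement 188 in total, so 94 per arm; 15% dropout; 220 randomised, so 110 per arm.

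**Step 1: rate in the acupuncture arm.** p2 = (0.15 × 1.9) / (0.85 + 0.15 × 1.9) = 0.285 / 1.135 = 0.2511. The difference is 0.1011 and the mean rate is 0.2006.

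**Step 2: attempt to reproduce 188.** With pooled variance under the null,

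n per arm = [1.960 × √(2 × 0.2006 × 0.7994) + 0.842 × √(0.15 × 0.85 + 0.2511 × 0.7489)]² / 0.1011²

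= (1.1099 + 0.4728)² / 0.010221 = 2.5047 / 0.010221 = 245.0.

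This is 490 in total, or 492 when each arm is rounded up to 246. The ratio to the stated figure is 492 / 188 = 2.6.

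**Step 3: other formulas and readings.**

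| Calculation | Total needed |
|---|---|
| Two-sided, unpooled variance | 486 |
| Two-sided, arcsine | 486 |
| Two-sided, log odds ratio | 502 |
| Two-sided, continuity-corrected | 530 |
| One-sided, pooled | 386 |
| 1.9 read as a risk ratio (15% vs 28.5%), two-sided pooled | 292 |
| 1.9 read as a risk ratio, one-sided pooled | 230 |
| OR 1.9, control rate 12% | 580 |
| OR 1.9, control rate 18% | 434 |
| OR 1.9, most favourable control rate (about 42%) | about 308 |

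None gives 188. The closest match is 188 per arm with a one-sided test (79.1% power), which contradicts the stated two-sided test, the word total and the 110 per group.

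**Step 4: power that the stated numbers deliver.** Power = Φ{[0.1011 × √n − 1.1099] / 0.5617}, where 0.5617 = √(0.1275 + 0.1880).

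- n = 94 per arm: (0.9802 − 1.1099) / 0.5617 = −0.231, so power is 40.9%. Exact enumeration of the chi-square test gives 41.2%.
- n = 110 per arm: (1.0604 − 1.1099) / 0.5617 = −0.088, so power is 46.5%. Exact enumeration gives 46.6%.
- n = 110 per arm with 15% missing in each arm counted as smoking: the rates become 0.85 × 15% = 12.75% and 0.85 × 25.1% = 21.3%, and power is 39.5%. This assumes that 15% and 25.1% are rates among participants with data and that missingness is equal in the two arms.

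**Step 5: effect detectable with 80% power at a 15% control rate.** With 94 per arm, 32.3% (OR about 2.7). With 110 per arm, 30.8% (OR about 2.5).

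**Step 6: joint success.** The probability that both outcomes are significant cannot exceed the probability that PPA is significant, so it is at most about 41% with 188 evaluable and 46% with 220. As an illustration only, VAS power of 80% and independence of the two outcomes would give 0.80 × 0.409 = 33% with 188 evaluable.

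**The case against.** A defence of 188 would have to come from a different formula, a different reading of 1.9, some latitude in a control rate described as approximate, or a gain from the GEE analysis. The table disposes of the first three. The fourth fails because the week-6 contrast has one binary value per participant, and the article claims no gain from covariates or repeated measures. Nor can a fuller protocol or analysis plan repair this, because the inputs and the result are both printed and they disagree.

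Several objections to side points do stand:

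- The dropout step is not an error worth raising: 188 / 0.85 = 221.2 against 220, and 220 × 0.85 = 187.
- The 39.5% figure is conditional. If the 15% planning rate already counts missing participants as smokers, the dilution would be counted twice, and 46% is the right figure for 110 per arm. The article does not say which applies.
- The craving claim is not shown to be wrong. An article may leave the effect size and SD to a fuller document, so only the PPA half of the statement in section 3.1 is refuted.
- The 33% joint figure uses two assumptions that are not in the document. Positive association between craving and abstinence would raise it. Only the upper bound follows from the article.
- The mismatch does not show which number is wrong. The odds ratio or the control rate may have been misreported, since 188 fits an odds ratio of about 2.7.

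**Conclusion.** The concern holds. The inputs in section 2.3 require about 490 evaluable participants (486 to 530 across standard two-sided formulas), not 188. Power for PPA at the planned effect is about 41% with 188 evaluable and at most about 46% with all 220, against the 80% stated. The PPA part of the adequate-power claim in section 3.1 fails for the same reason, and the both-must-win rule caps the chance of a positive trial at the PPA power.

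This rests only on the control rate, odds ratio, alpha, power and allocation printed in section 2.3. It does not depend on the dilution or joint-power illustrations. It must be corrected because the main sizing statement for a co-primary outcome is wrong as written.

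**What to change.** The sponsor should first check the original calculation and establish which figure is in error: the odds ratio, the control rate or the total.

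- **If the inputs and 220 are both kept:** replace the 80% and 188 statement in section 2.3. State that 220 randomised gives about 41% power (188 evaluable) to 46% (all 220 evaluable) for OR 1.9 at 15% control abstinence, and 80% power only for an odds ratio of about 2.5 to 2.7. Say whether the planning rates already count missing participants as smokers; if they do not, power is about 40%.
- **Craving outcome:** give the standardised difference detectable with 80% power, (1.960 + 0.842) × √(2/n), which is 0.41 with 94 per arm and 0.38 with 110. State the joint power for winning on both outcomes, with its assumptions.
- **Section 3.1:** delete the claim of adequate power for both co-primary outcomes. State in advance that a non-significant PPA result will be interpreted from its confidence interval.

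This costs rewording of two sections and a less favourable stated power, with no extra participants. Keeping 80% power at OR 1.9 is a different decision: it needs about 492 evaluable, or 492 / 0.85 = 579 randomised. If an input was misreported, the corrected value should be given with its source and the calculation redone.

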### Statistical analysis

2.10

An independent statistician contributed to the development of the statistical analysis plan and the sample size calculation. This statistician, who will remain blinded to group allocation and not involved in study conduct, will perform all analyses according to the pre-specified plan. All analyses will be conducted according to the intention-to-treat (ITT) principle, including all randomized participants in their assigned groups.

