#### Two co-primary outcomes will be analyzed as follows

2.10.1

Multiplicity control for co-primary outcomes. Type I error is controlled at the family-wise level using the Hochberg procedure. The trial will be declared positive only if both co-primary outcomes (VAS craving change and PPA at week 6) achieve statistical significance at *p* ≤ 0.05.

The change in nicotine craving intensity measured by the VAS from baseline to week 6 (one of the two co-primary outcomes) will be analyzed using linear mixed-effects models including fixed effects for group, time, and group × time interaction, with participant-specific random intercepts to account for repeated measurements.

The PPA at week 6 (the second co-primary outcome) will be analyzed using generalized estimating equations (GEE) with a logit link function and an exchangeable correlation structure. Results will be reported as adjusted odds ratios (ORs) with 95% confidence intervals (CIs).

For smoking abstinence outcomes, missing smoking-status data will be treated as non-abstinent in the primary analysis. For sensitivity analysis, a pattern mixture model under missing-not-at-random (MNAR) assumptions will be applied, assuming a relapse rate of 80–90% among participants with missing follow-up data (42).

Secondary continuous outcomes will be analyzed using linear mixed-effects models, including fixed effects for group, time, and group × time interaction, and random intercepts to account for within-subject correlation. Models will be adjusted for baseline values where appropriate. SF-36 total scores and PSQI global scores will be analyzed directly, with similar models applied to BDI-II, BAI, and exhaled carbon monoxide (CO).

To control for type I error due to multiple comparisons across the secondary outcomes (BDI-II, BAI, SF-36, PSQI, CO), a false discovery rate (FDR) procedure will be applied. Adjusted *p*-values will be reported alongside unadjusted estimates, and findings will be interpreted with appropriate caution (43).

Prespecified subgroup analyses will include three-way interaction terms (subgroup × treatment × time) within mixed-effects models to explore potential effect modification by sex (male/female) and age (<40 vs. ≥40 years).

Sensitivity analyses will include a per-protocol (PP) analysis excluding participants with less than 80% adherence, defined as attendance at fewer than 14 of 18 acupuncture sessions or NRT use on fewer than 80% of study days.

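### The 80% power stated for week-6 abstinence is not computed for the planned analysis, which keeps all 220 randomised participants and counts missing as non-abstinent

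*Protocol article*

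**What the plan says.** Section 2.3 of the protocol article names the outcome that drives the size: "The sample size was calculated based on the co-primary outcome of 7-day point prevalence abstinence (PPA) at week 6". The inputs follow: "a control group abstinence rate of approximately 15% was assumed", "with an odds ratio (OR) of 1.9 for the HMA + NRT group". The result is given as "With a two-sided significance level of *α* = 0.05, 80% power, and a 1:1 allocation ratio, a total of 188 participants is required", and then "Accounting for a 15% dropout rate, the final sample size is set at 220 participants (110 per group"). The section does not say whether the 15% rate and the OR refer to participants with a known smoking status or to everyone randomised with missing counted as smoking.

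The analysis sections handle dropouts differently. Section 2.10 applies intention to treat, "including all randomized participants in their assigned groups". Section 2.10.1 adds that "missing smoking-status data will be treated as non-abstinent in the primary analysis". Section 3.1 then describes 220 as adequate for both co-primary outcomes.

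**The concern.** Dividing a required number by 0.85 makes sense when a dropout supplies no outcome, so that 220 enrolled leaves about 188 to analyse. Under the rule in 2.10.1 no one leaves the abstinence analysis. The analysed number is 220, and each dropout enters as a failure. One endpoint is therefore sized under one treatment of dropouts and analysed under another.

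What this means depends on what the planning rates are:

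- If they are completer rates, both analysed rates are lower than stated, and so is their difference.
- If they already count missing as smoking, the abstinence outcome needs no dropout inflation and its power should be computed at 220, not 188.

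On neither reading is the stated 80% the power of the analysis that will be run. The rule also makes the tested effect depend on how dropout splits between the arms, which a single 15% inflation cannot reflect.

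**Working it through.** **Inputs.** Control rate 15%, OR 1.9, two-sided 0.05, 80% power, 1:1, 188 before and 220 after 15% dropout (Section 2.3); all randomised analysed (2.10); missing = non-abstinent (2.10.1). Equal dropout in both arms is assumed unless stated.

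**The plan's own figures.** HMA + NRT odds = 1.9 × 0.15/0.85 = 0.3353, so the rate is 0.3353/1.3353 = 25.1%. The dropout step nearly reproduces: 188/0.85 = 221.2, against 220 stated. The base does not. With p̄ = (0.15 + 0.2511)/2 = 0.2006,

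n per arm = [1.96·√(2p̄(1−p̄)) + 0.8416·√(p₁(1−p₁) + p₂(1−p₂))]² / (p₂−p₁)² = [1.96 × 0.5663 + 0.8416 × 0.5617]² / 0.1011² ≈ 245.05,

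which rounds up to 246 per arm, 492 in total. Unpooled, arcsine and log-OR versions give 486 to 502, and a continuity correction gives 530. One-sided versions give 382 to 426. Reading 1.9 as a risk ratio gives 292, or 230 one-sided. None gives 188.

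**Power formula.** Power = Φ{[(p₂−p₁)√n − 1.96·√(2p̄(1−p̄))] / √(p₁(1−p₁) + p₂(1−p₂))}, with n per arm.

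**Effect of the analysis rule if the rates are completer rates.** Multiply each rate by 0.85: 0.15 × 0.85 = 12.75%; 0.2511 × 0.85 = 21.3%. The difference falls from 10.1 to 8.6 points. OR = (0.2134/0.7866)/(0.1275/0.8725) = 1.86.

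| Scenario | n per arm | Rates | Power |
|---|---|---|---|
| Completers only | 94 | 15% vs 25.1% | 40.9% |
| Planned rule, with the allowance | 110 | 12.75% vs 21.3% | 39.5% |
| Planned rule, without the allowance | 94 | 12.75% vs 21.3% | 34.6% |
| Rates already count missing as smoking | 110 | 15% vs 25.1% | 46.5% |

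The second row worked through: Φ{[0.0859 × √110 − 1.96 × 0.5318]/0.5283} = Φ(−0.267) = 39.5%.

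**How much the allowance recovers.** Without it, power falls 40.9 − 34.6 = 6.3 points. With it, the fall is 40.9 − 39.5 = 1.4 points. For equal dropout from 5% to 25%, the loss ranges from 0.4 to 1.8 points. From a base of 492 the picture is the same: 492/0.85 = 579 randomised gives 78.7% under the planned rule, against 80.2% for 492 completers. Sizing directly on the diluted rates gives 600.

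**Where the shortfall comes from (completer reading).** From 80% to 40.9% (39.1 points) is the base number. From 40.9% to 39.5% (1.4 points) is the dropout mismatch.

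**Unequal dropout.** These splits are assumed, since the protocol gives only one overall rate; the rates are taken as completer rates, with 110 per arm.

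- 10% control, 20% HMA: 0.15 × 0.90 = 13.5% vs 0.2511 × 0.80 = 20.1%; OR 1.61, power 25.6%.
- 20% control, 10% HMA: 0.15 × 0.80 = 12.0% vs 0.2511 × 0.90 = 22.6%; OR 2.14, power 54.8%.

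**The case against.** The strongest reply is that the allowance works nearly as intended. With equal dropout it leaves a gap of about 1.4 points, and an OR change of 0.04 is well inside the uncertainty of an approximate 15% taken from reviews. That stands. A reader might infer from the mismatch that the allowance fails to protect power, or that the target effect is materially diluted. The figures do not support either inference under equal dropout.

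It is also fair that Section 2.3 never says dropouts will be removed from the abstinence analysis, nor that its rates are completer rates. Dilution is therefore conditional. If the rates already count missing as smoking, nothing is diluted and using 188 understates the analysed number.

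The analysis sections agree with each other, so the analysis population is not in doubt. Enlarging recruitment for attrition is ordinary practice, and the same 220 serves the craving outcome, for which a dropout does lose the week-6 value. The unequal splits are illustrations, with no evidence in the protocol that dropout will be unequal.

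What the reply does not remove is that the protocol states a power for this endpoint and that figure is not the power of the stated analysis on either reading of the rates.

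**Conclusion.** The mismatch between Section 2.3 and Sections 2.10 and 2.10.1 is real, and the 80% claim for abstinence does not describe the planned analysis. Under the planned rule, 220 randomised gives about 39% power if the planning rates are completer rates with 15% dropout in each arm, and about 46% if they already count missing as smoking. These figures rest on the stated 15% and OR 1.9 and on a normal-approximation test of two proportions.

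The size must be attributed correctly. A reader might blame the dropout step for power of about 39%; its own share is about 1.4 points under equal dropout. The rest arises because 188 does not follow from its inputs. The one place where the dropout rule could matter substantially is unequal loss between the arms, which the inflation does not address and which remains an assumption here.

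**What to change.** In Section 2.3:

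- State whether 15% and OR 1.9 are completer rates or already count missing as smoking.
- Replace the 188-to-220 step for abstinence with the power for all 220 randomised under the 2.10.1 rule, using 12.75% vs 21.3% in the first case (about 39%) or 15% vs 25.1% in the second (about 46%).
- Apply the 15% allowance to the VAS craving outcome only.

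In Section 3.1, change the adequate-power statement to match. A short table of power under unequal dropout would be useful but is optional.

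The cost is protocol wording and one recalculation, with a much lower stated power as the result. This correction needs no extra participants and no change to the analysis. When the base number of 188 is itself corrected, dividing the new base by 0.85 would carry the same mismatch forward, so the new figure should be computed directly under the 2.10.1 rule.

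### The 80% power is for week-6 abstinence alone, but the trial succeeds only if craving is significant too; the adequate-power claim is not supported for that rule

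*Protocol article*

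**What the plan says.** Section 2.3 (Randomization, blinding and sample size) ties the calculation to one endpoint: "The sample size was calculated based on the co-primary outcome of 7-day point prevalence abstinence (PPA) at week 6". Its inputs are "a control group abstinence rate of approximately 15% was assumed" and "with an odds ratio (OR) of 1.9 for the HMA + NRT group". The result is: "With a two-sided significance level of *α* = 0.05, 80% power, and a 1:1 allocation ratio, a total of 188 participants is required". This is raised to 220 (110 per arm) for 15% dropout.

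On the other co-primary, the same section says only: "The VAS craving outcome, as the other co-primary endpoint, is also adequately powered based on the same sample size". No VAS difference, SD or power value accompanies it. Section 3.1 (Limitations) restates the position: "the sample size of 220 provides adequate power for both co-primary outcomes".

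The success rule is in section 2.3 and again in section 2.10.1: "The trial will be declared positive only if both co-primary outcomes" reach p ≤ 0.05. Section 2.3 uses this requirement to justify testing each outcome at the full 0.05.

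**The concern.** When two tests must both succeed, the power that matters is the probability that both do. It cannot exceed the smaller of the two single-endpoint powers, and it falls below that unless the other test is almost certain to succeed. The plan takes the type I benefit of the both-required rule (no split of alpha) but does not count its type II cost. Its only power figure, 80%, belongs to one of the two required tests.

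At stake is how a miss would be interpreted. If one outcome fails, a reader relying on the Limitations section could take this as a negative result from an adequately powered trial, although the rule that produced it was never sized.

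**Working it through.** **Step 1. The plan's own figure.**

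Inputs (section 2.3): p1 = 0.15, odds ratio 1.9, two-sided α = 0.05, power 80%, 1:1 allocation.

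- Treated odds = 1.9 × 0.15/0.85 = 0.3353, so p2 = 0.3353/1.3353 = 0.2511. The difference is 0.1011 and the mean rate 0.2006.
- n per arm = [1.96·√(2·p̄·q̄) + 0.8416·√(p1q1 + p2q2)]² / (p2 − p1)² = [1.96 × 0.5663 + 0.8416 × 0.5617]² / 0.1011², which gives 246 per arm, or 492 in total. The plan prints 188.
- Other two-sided forms (unpooled, arcsine, log odds ratio, continuity-corrected) give 486 to 530. One-sided forms give 382 to 426. Reading 1.9 as a risk ratio gives 286 to 320 two-sided and 226 to 258 one-sided. None gives 188.
- The dropout step is not the problem: 188/0.85 = 221.2, against the stated 220.

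**Step 2. PPA power at the plan's numbers.**

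Power = Φ{[0.1011·√n − 1.96 × 0.5663] / 0.5617}.

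- n = 94 per arm (188/2): Φ(−0.23) = 40.9%.
- n = 110 per arm: Φ(−0.09) = 46.5%.
- n = 110 per arm with 15% missing in each arm, counted as non-abstinent as section 2.10.1 specifies: rates become 0.85 × 0.15 and 0.85 × 0.2511, and power is 39.5%.

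**Step 3. Joint power, accepting the printed 80% for PPA.**

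Joint power = P(Z1 ≤ Φ⁻¹(power PPA), Z2 ≤ Φ⁻¹(power VAS)), bivariate normal with correlation ρ. At ρ = 0 this is the product, for example 0.80 × 0.80 = 0.64. Both ρ and VAS power are assumptions, since the document gives neither.

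| VAS power | ρ = 0 | 0.2 | 0.4 | 0.6 |
|---|---|---|---|---|
| 80% | 64.0% | 65.7% | 67.6% | 69.9% |
| 90% | 72.0% | 73.1% | 74.4% | 76.0% |
| 95% | 76.0% | 76.7% | 77.5% | 78.4% |
| 99% | 79.2% | 79.4% | 79.6% | 79.8% |

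**Step 4. Joint power with the recomputed PPA power.**

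For VAS power from 80% to 99% and ρ from 0 to 0.8:

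- 94 per arm: 32.7% to 40.9%.
- 110 per arm: 37.2% to 46.5%.

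The upper ends are the PPA powers from step 2. No VAS effect, however large, can lift the joint figure above them.

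**Step 5. What VAS power would require.**

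For an unadjusted two-sample comparison at 94 per arm, a standardised difference of 0.30 gives 54% power, 0.41 gives 80%, 0.50 gives 93% and 0.60 gives 98%. These are for orientation only. Section 2.10.1 plans a repeated-measures mixed model, whose power may differ.

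**The case against.** The strongest reply is that the wording about power is marginal. The sentence in section 2.3 speaks of VAS on its own, and the one in section 3.1 can be read as each outcome separately. The document never claims 80% for the two together. That is fair, and it limits the point. A reader might infer that the VAS statement is false and that craving is underpowered. The document does not support that: without a VAS difference or SD the statement is unsupported, not disproved.

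A reader might also infer that the both-required rule must cost many points of power by itself. On the printed 80% for PPA, the loss depends on an unknown. It is 10 to 16 points at VAS power 80%, but only 2 to 4 at 95% and under 1 at 99%.

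It can also be said that an article may leave the VAS effect and a joint-power calculation to the full protocol or SAP. Their absence alone would indeed be no finding. What remains is that the article itself prints a one-endpoint calculation, a two-endpoint success rule and a conclusion of adequacy, and the first does not support the last under the second.

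Finally, the failure of 188 to follow from its inputs is a separate and larger defect. That is true, but correcting it alone would still leave the success rule without a stated power.

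**Conclusion.** The point stands in limited form. The plan's 80% is a target for PPA alone, the trial needs both outcomes, and the adequacy wording in sections 2.3 and 3.1 is not supported for that rule.

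The size has two layers. With the printed 80% taken at face value, joint power runs from 64% to just under 80%, depending on assumed VAS power (80% to 99%) and assumed correlation (0 to 0.6). With the PPA power that follows from 15% and an odds ratio of 1.9, joint power is capped at about 41% (94 per arm) or 46% (110 per arm). This second result needs no assumption about VAS or correlation. It rests only on the plan's PPA inputs and a standard two-proportion test. The 64–80% range should therefore not be read as endorsing the printed 80%, and nothing here shows that 220 is enough.

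**What to change.** In section 2.3:

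- say that 80% was the target for PPA alone;
- recompute PPA power from 15% and an odds ratio of 1.9;
- give the VAS difference and SD behind the craving claim, with the resulting power;
- report the probability that both tests are significant at 220 randomised, over a stated correlation range such as 0 to 0.6.

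In section 3.1, delete the statement that "the sample size of 220 provides adequate power for both co-primary outcomes" unless the joint figure bears it out, and do not describe 220 as adequate in its place.

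The work is a short calculation and a few sentences. The cost is a less favourable stated power, well below 80% if the PPA assumptions are kept.
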